# The effects of aerobic exercise on body composition in overweight and obese patients with gout: a randomized, open-labeled, controlled trial

**DOI:** 10.1186/s13063-022-06695-x

**Published:** 2022-09-05

**Keywords:** Gout, Body composition, Treadmill exercise test, Aerobic exercise, Randomized controlled trial

## Abstract

**Background:**

Overweight and obesity are typical risk factors for the increased prevalence and incidence of gout. The existing guidelines unequivocally indicated that exercise is highly advantageous for patients with gout. Nevertheless, there is still a lack of specific guidance and clinical evidence. The effects of exercise on improving gout, and the optimal frequency, timing, and types of exercise have not been fully clarified. The present trial aims to determine the effects of a specific aerobic exercise program on body composition in overweight and obese patients with gout.

**Methods:**

In this randomized, open-labeled, controlled trial, a total of 60 overweight and obese patients with gout [body mass index (BMI) ≥ 24 kg/m^2^; age,18–55 years old] are equally randomized (1:1) into two groups (*n* = 30): moderate-intensity aerobic exercise group (MIAEG), heart rate reserve (HRR) = [(HRmax-HRrest) × 60% intensity] + HRrest, and control group (CG). The moderate-intensity aerobic exercise training program will be conducted for 30–40 min/session and 3 days/week for 12 weeks. Participants in the CG will be asked to avoid making changes in their exercise habits. There will be no limitation in the type of exercise. The primary outcome is the number of patients whose body fat is reduced after 12 weeks. The secondary outcomes include the changes in BMI, waist-to-hip ratio (WHR), insulin resistance index (IRI), serum uric acid (sUA), serum creatinine (SCr), estimated glomerular filtration rate (eGFR), triglycerides (TG), total cholesterol (TC), low-density lipoprotein cholesterol (LDL-C), high-density lipoprotein cholesterol (HDL-C), hepatic steatosis, and adverse effects after 12 weeks. One-way analysis of variance (ANOVA) will be used to compare the mean values of normally distributed variables between MIAEG and GC.

**Discussion:**

The effect and optimal frequency of exercise for improving the status of overweight and obese patients with gout have not yet been determined. We design a 12-week randomized controlled trial and evaluate the effects of individualized aerobic exercise program on patients with gout. The results may assist such patients with a personalized scientific exercise program based on the disease status and motor abilities, so that patients are prone to exercise under the condition of low risk and achieve the greatest benefits.

**Trial registration:**

ChiCTR2200062153. Registered on July 25, 2022, with ChiCTR. http://www.chictr.org.cn/

## Introduction

### Background and rationale {6a}

Gout is mainly a metabolic syndrome caused by purine metabolism disorder, and uric acid (UA) excretion disorder and (or) increased UA production is one of the leading causes of purine metabolism disorder. A meta-analysis reported that the overall prevalence of gout in China was 1.1%, and its prevalence among men (1.5%) was higher than that among women (0.9%). Besides, gout has become the second most common metabolic disease after diabetes [1]. In the recent 20 years, improvement in living standards and changes in lifestyle and diet plan have led to the remarkably increase of the incidence of gout. The age of onset of gout has gradually become younger. There is a consensus that hyperlipidemia, hypertension, and type 2 diabetes are more prevalently detected in patients with gout [2]. These diseases all belong to the subgroups of metabolic syndrome. Gout and the subgroups of metabolic syndrome are reciprocal causation, influence each other, exacerbate the illness, and even substantially increase the risk of cardiovascular disease.

At present, the gout is known to be associated with purine metabolism disorder, serum UA (sUA) metabolism disorder, diet and lifestyle, and is affected by genetic and environmental factors. Overweight and obesity were reported as typical risk factors for the increased prevalence and incidence of gout [3]. In a Mendelian randomization study, a higher body mass index (BMI) was positively correlated with the risk of gout and sUA concentration. Each standard deviation (about 4.6 kg/m^2^) increase in BMI was associated with an odds ratio (OR) of 2.24 for gout and with a 0.30 mg/dl increase in sUA level [4]. Intervention with bariatric surgery, which prevented gout and hyperuricemia in obese subjects, reduced the incidence of gout by 40% over 26 years of follow-up [5].

Moderate-intensity and regular physical exercise can significantly contribute to the long-term survival of patients with gout. A study demonstrated that light- and moderate-intensity exercises cause anti-inflammatory effects to varying degrees. Nuclear factor-κB (NF-κB) activity, synovial infiltration by macrophages and neutrophils, Toll-like receptor 2 (TLR2) expression level in peripheral neutrophils, and chemokine ligand 1 (CXCL1) expression level in serum were downregulated after light- and moderate-intensity exercises [6]. Additionally, aerobic exercise decreases sUA level by accelerating ATP turnover rate (indicated by the increase in serum phosphorus level and the decrease in serum levels of ATP, adenosine, and hypoxanthine) [7], whereas exercise is a double-edged sword with dual effects on the body. It is noteworthy that the body would accelerate the degradation of purine nucleotide and generate a large amount of lactic acid during anaerobic exercise, and the accumulated lactic acid would affect the excretion of UA by the kidney, associating with the increase of UA concentration and the likelihood of gout flares [8]. Vigorous exercise greatly increases the serum antioxidant capacity and also causes a short-term increase in UA level [9]. Hence, the effects of intensity and frequency of the certain modality of exercise, along with duration of the exercise on disease are various. Aerobic exercise such as brisk walking, jogging, cycling, and Tai chi is often a preferred mode of exercise due to its simplicity and practicality than engage in vigorous exercise.

The guidelines unequivocally indicated that exercise is one of the non-pharmacological measures for patients with gout [10–12]. Nevertheless, there is still a lack of specific guidance and clinical evidence, and the effects of exercise on improving gout and the optimal frequency, timing, and type of exercise have not been fully clarified. Gout is a continuous, chronic pathological process that requires long-term and even lifetime health care, while chronic disease management of gout is still suboptimal in several countries. The primary reason for patients' insufficient exercise participation is that the disease itself has a noticeable influence on the exercise capacity, resulting in loss of patients’ confidence in exercise. A vicious circle is eventually developed. Thus, selection of a valid and adherence of exercise program has attracted rheumatologists’ attention. Moderate-intensity aerobic exercise does not cause remarkable fluctuations in lactic acid concentration and affects UA excretion in patients with a lower risk of gout. Treadmill exercise test (TET) is a scientific assessment of exercise tolerance based on metabolic equivalent (METs). The target heart rate and exercise speed of patients with gout will be assessed by the Heart rate reserve method and Bruce protocol, respectively [13]. The aim is to provide data support for the development of personalized exercise prescriptions as well as provides a bottom line for exercise risks.

### Objectives {7}

The present trial aims to determine the effects of a specific aerobic exercise program on body composition in overweight and obese patients with gout.

### Trial design {8}

This is a randomized, open-label, controlled trial over 12 weeks. A total of 60 patients with gout who meet the study criteria are randomized (1:1) to the moderate-intensity aerobic exercise group and control group (Fig. 1). The trial framework is exploratory.

**Fig. 1 Fig1:**
[figure not shown]
Trial flow and study design

## Methods: participants, interventions, and outcomes

### Study setting {9}

The present study will be completed at Shenzhen Traditional Chinese Medicine Hospital, People’s Hospital of Longhua District Shenzhen, and the Second Affiliated Hospital of Guizhou University of Traditional Chinese Medicine from May 16, 2022, to May 16, 2024. Written informed consent is obtained from all participants prior to the commencement of the study. All enrolled participants will be fully informed about the objective, methods, and possible risks of the study.

### Eligibility criteria {10}

#### Inclusion criteria

Patients who meet the following criteria will be included:Male or female patients aging 18–55 years old;BMI ≥ 24 kg/m^2^;The diagnosis meets the 2015 European League Against Rheumatism (EULAR)/American College of Rheumatology (ACR) criteria for gout;The absence of gout flares in the last 2 weeks;Patients with complete clinical data who voluntarily participate in the study and sign the informed consent form.

### Who will take informed consent? {26a}

The subjects in this study will be recruited from outpatient and inpatient wards by placing advertisements on social media platforms of the hospital departments and distributing posters in public areas of the hospital with details of the study and contact information. Patients who meet the criteria will be invited to participate in the study, and they will be provided with the details of the RCT protocol. All subjects will be required to sign an informed consent by the clinicians.

### Additional consent provisions for collection and use of participant data and biological specimens {26b}

We will request consent for review of participants’ medical records, and for the collection of blood samples to assess insulin resistance index (IRI), serum uric acid (sUA), serum creatinine (SCr), estimated glomerular filtration rate (eGFR), triglycerides (TG), total cholesterol (TC), low-density lipoprotein cholesterol (LDL-C), and high-density lipoprotein cholesterol (HDL-C).

### Interventions

#### Explanation for the choice of comparators {6b}

A total of 60 patients who are overweight and obese patients with gout who meet the study criteria will be randomized (1:1) to the moderate-intensity aerobic exercise group and control group.

#### Intervention description {11a}

Control group

Participants in the control group will be given general health education, including knowledge about regular exercise, moderate water intake, restriction of alcohol consumption, and high sugar and purine diet intake. Participants will be asked to avoid making changes in their exercise habits during the study. There is no limit to the method of exercise.(2)Moderate-intensity aerobic exercise group

Aerobic exercise refers to the physical exercise of low to high intensity that depends primarily on the aerobic energy-generating process. “Aerobic” is defined as “relating to, involving, or requiring oxygen,” and refers to the use of oxygen to meet energy demands during exercise via aerobic metabolism adequately. Examples of aerobic exercise include medium- to long-distance running or jogging, swimming, cycling, stair climbing, and walking. On the basis of general health education, moderate-intensity aerobic exercise will be prescribed with METs using a treadmill exercise test system (T2100-ST2; GE Healthcare, Waltham, MA, USA) and an automated sphygmomanometer (SunTech Medical Tango M2; SunTech Medical, Inc., Morrisville, NC, USA). The target HR and exercise speed of patients with gout will be assessed by the HR reserve and Bruce protocol, respectively. The Karvonen method will be used to target an exercise intensity of 60% of HR reserve as follows: HRR= ((HRmax-HRrest) × Intensity (%)) + HRrest, where the maximum HR (HRmax) uses the submaximal HR [85%×(220-age)] during the exercise tests. Exercise tests will be performed according to the Bruce protocol. Therefore, the target HR calculated by the HR reserve method will be used as the target HR of moderate-intensity aerobic exercise. The speed of aerobic exercise corresponding to the MET value of target HR calculated by the HR reserve method will be used as the main exercise program of the test group (Table 1). If participants cannot tolerate running, the mode will be switched to cycling. At the same time, aerobic exercise of reasonable intensity is determined by evaluating subjective physical sensation with the Borg rating of perceived exertion (RPE) scale (Table 2) [14]. For the moderate-intensity aerobic exercise session, which is corresponded to RPE of “12–13,” it is recommended to exercise for 30–40 min/session (excluding warm-up and stretching), 3–5 times/week, and maintain 120–150 min/week. The venue includes sidewalks, parks, gyms, and other appropriate places for exercise.(3)Trial period

**Table 1 Tab1:** Energy expenditure levels of running and cycling

Energy expenditure levels	3∼4 METs	5∼6 METs	7∼8 METs	>9 METs
Mode				
Running (km/h)	4.8-6.4	7.2-8.0	8	10
Cycling (km/h)	13	14.5-16.0	19	>21

**Table 2 Tab2:** Borg rating of perceived exertion scale

RPE	subjective feeling	reference heart rate
6	ease	HRrest
7	very, very light	70 bpm
8		
9	very light	90 bpm
10	fairly light	
11		110 bpm
12	somewhat hard	
13		130 bpm
14		
15	hard	150 bpm
16	very hard	
17		170 bpm
18		
19	very, very hard	195 bpm
20		HRmax

1–12-week: HRR=((HR_max_-HR_rest_)×60% intensity)+HR_rest._ The target HR calculated by the HR reserve method will be used as the target HR of moderate-intensity aerobic exercise. The exercise speed of patients with gout corresponding to the MET value of target HR calculated by the HR reserve method will be used as the main exercise program in the test group.

During the trial, (1) all participants will receive general administration of gout, (2) all participants will be asked to avoid making changes in their dietary habits, (3) participants should keep records of training sessions during the whole intervention, and (4) participants will be asked to avoid performing exercise after drinking or after taking sedatives and analgesics.

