### Outcomes {12}

#### Primary outcome

Primary outcome will include the number of patients whose body fat is reduced after 12 weeks.

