### Statistical methods

#### Statistical methods for primary and secondary outcomes {20a}

Statistical analysis will be carried out using SAS 9.4 statistical software, and all data will be expressed as mean ± standard deviation (SD) or percentage (%). Differences in demographic data, anthropometric measurement, blood biochemical parameters, and health-related physical fitness components between baseline and week 12 groups will be analyzed using the paired *t*-test. One-way analysis of variance (ANOVA) will be used to compare the mean values of normally distributed variables between MIAEG and GC. Statistical analysis was carried out using SPSS (version 26). A two-tailed significance level of 0.05 was used for all tests. *P* < 0.05 is considered statistically significant.

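### The diet instructions given to both arms conflict, and, separately, the planned paired tests cannot isolate the effect of exercise

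*Protocol article*

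**What the plan says.** Four places in the protocol article bear on this.

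- **Intervention description {11a}, control group.** Controls receive "general health education, including knowledge about regular exercise, moderate water intake, restriction of alcohol consumption, and high sugar and purine diet intake".
- **Intervention description {11a}, exercise group.** The same education underlies the exercise arm: "On the basis of general health education, moderate-intensity aerobic exercise will be prescribed with METs".
- **Intervention description {11a}, conditions during the trial.** For both arms, "all participants will be asked to avoid making changes in their dietary habits".
- **Statistical methods for primary and secondary outcomes {20a}.** Differences in demographic, anthropometric, biochemical and fitness measures "between baseline and week 12 groups will be analyzed using the paired" t-test. The next sentence plans a one-way ANOVA to "compare the mean values of normally distributed variables between MIAEG and GC". A two-sided 0.05 level applies to all tests.

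The objective (Objectives {7}) is to "determine the effects of a specific aerobic exercise program on body composition in overweight and obese patients with gout". The primary outcome is "the number of patients whose body fat is reduced after 12 weeks". Allocation is randomised 1:1 and the framework is described as exploratory (Trial design {8}).

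**The concern.** There are two separate points.

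**The diet instruction.** Education on restricting alcohol, sugar and purines invites a change from anyone whose intake is high at enrolment. The later instruction asks the same person to change nothing. Staff at three hospitals have to decide which one to enforce. The background care against which exercise is tested is therefore not clearly defined.

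**The paired tests.** The objective concerns the effect of the exercise programme. A change from baseline within the exercise arm contains the exercise effect, any response to the shared advice, and anything else that moves with time, such as regression to the mean. A significant paired test is therefore no evidence that exercise did anything. The section sets these tests beside the between-arm ANOVA at the same 0.05 level and gives them no lesser standing. At stake is a report in which a significant change in the exercise arm, perhaps with a non-significant one in controls, is taken as an exercise effect.

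**Working it through.** **Step 1. The instructions side by side.**

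| Element | Control arm | Exercise arm |
|---|---|---|
| Education covering alcohol, sugar and purines | Yes | Yes, exercise is added to it |
| Request not to change diet | Yes | Yes |
| Prescribed aerobic exercise | No | Yes |

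For a participant with high intake, rows one and two conflict. Both rows are the same in the two columns, so any mean response to them is expected to cancel in the difference between arms. What remains is exercise added to health education.

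**Step 2. Inputs for the paired tests.**

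- From the protocol (Sample size {14}): 25 evaluable patients per arm, 15% dropout, 30 per arm enrolled. The dropout step reproduces: 25 / (1 − 0.15) = 29.4, rounded up to 30.
- From the protocol (Statistical methods {20a}): two-sided 0.05.
- Assumed, because the protocol gives no figure: exercise has no effect; both arms share a mean change of d standard deviations of the change, with d = 0.25, 0.5 or 0.75; changes are normal; the arms are independent.

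**Step 3. Within-arm test.** The paired t statistic has a noncentral t distribution with n − 1 degrees of freedom and noncentrality d√n. The critical value is 2.064 for n = 25 and 2.045 for n = 30.

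| Shared change d | d√25 | Significant, n = 25 | d√30 | Significant, n = 30 |
|---|---|---|---|---|
| 0.25 | 1.25 | 22% | 1.37 | 26% |
| 0.5 | 2.50 | 67% | 2.74 | 75% |
| 0.75 | 3.75 | 95% | 4.11 | 98% |

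**Step 4. Between-arm test.** The expected difference in change is d − d = 0 for every d, so the test keeps its 5% level. A simulation of 20,000 trials with n = 25 gave 5.1%, 5.0%, 5.0% and 4.9% at d = 0, 0.3, 0.5 and 0.8.

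**Step 5. Exercise arm significant, control arm not.** With p from Step 3 at n = 25, the probability is p(1 − p):

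- d = 0: 0.05 × 0.95 = 4.75%
- d = 0.25: 0.224 × 0.776 = 17%
- d = 0.5: 0.670 × 0.330 = 22%
- d = 0.75: 0.949 × 0.051 = 5%

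The mirror pattern, control arm only, is equally likely. The excess over 4.75% appears at small to moderate shared changes and is gone by 0.75 SD, where both arms are usually significant.

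**The case against.** The strongest reply is that neither point damages the randomised comparison. Both arms get the same education and the same diet request, a between-arm ANOVA is planned in the sentence after the paired tests, and the section on additional analyses adds a logistic regression with odds ratios. Nothing in the article says that efficacy will be concluded from paired results. The paired tests concern continuous measures, not the primary outcome, which is a count. Which test carries the inference is often left to the analysis plan. The diet wording can also be softened: the education conveys knowledge and sets no dietary prescription, and its timing relative to baseline is not given. Finally, the shared changes are assumed, and the paired-test percentages would hold with no diet conflict at all.

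Most of this stands. The contrast is unbiased, the two points are separate, and the percentages do not measure the diet conflict. Two things survive. The article states two instructions that a high-intake participant cannot both follow. It also states a test that cannot answer its own objective. Neither is an omission left to another document.

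Two stronger readings are tempting. A reader might infer that the diet conflict biases the trial's comparison; the documents do not support that, because the conflict is common to both arms. A reader might also infer that a shared diet response must dilute the primary endpoint, since it has no stated threshold. Whether it would depends on the control responder rate, which the protocol does not give, so no dilution figure is offered as evidence.

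**Conclusion.** The concern holds in limited form. The diet instructions contradict each other for participants with high intake and should be reconciled, but the between-arm contrast remains valid for exercise added to health education. The paired tests cannot support a conclusion about exercise. With 25 per arm, no exercise effect and an assumed shared change of 0.25 to 0.75 SD, they are significant in 22% to 95% of trials, while the between-arm test stays at 5%. These figures show how a paired test behaves under those assumptions; they do not predict this trial, since the size of any advice or time effect is unknown. The exploratory framework lowers the stakes, but it does not let a within-arm change demonstrate an exercise effect. A correction is worth making, and confidence in the point is medium.

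**What to change.** 1. Replace the two diet statements with one instruction, identical in both arms: for example, standard gout advice at enrolment, then keep to that diet for the 12 weeks. This removes the contradiction. It does not guarantee that no diet response falls within the 12 weeks, which is one reason the second change is needed regardless.
2. State in the statistical methods that conclusions rest only on the between-arm contrast, worded as the effect of exercise added to health education, and that the paired tests are descriptive.

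Optional: give the education before baseline measurement, and record a brief diet and alcohol item at the three existing visits if the full protocol does not already do so. The first changes procedure at three sites and the second lengthens visits slightly. Neither is needed for the correction.

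Cost: a small wording amendment, which needs ethics approval under the protocol's own amendment procedure. Within-arm P values can no longer support efficacy claims.

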### Research procedures

Screening

According to the ACR/EULAR criteria and the scoring system for gout presented in 2015, we will adopt the following criteria: patients with gout (in intermittent or chronic phase; there will be no gout flare in the last 2 weeks); patients aging 18–55-years-old; patients with BMI ≥ 24 kg/m^2^.(2)Enrollment

Participants will be randomly assigned into test and control groups, and participants in both groups will be treated for 12 weeks.(3)Program

Moderate-intensity aerobic exercise group:

The target HR calculated by the HR reserve method will be used as the target HR in the moderate-intensity aerobic exercise. The exercise speed of patients with gout corresponding to the MET value of target HR calculated by the HR reserve method will be utilized as the main exercise program in the test group. The HR reserve will be calculated as follows: HRR = [(HRmax-HRrest) × 60% Intensity] + HRrest. The exercise will be performed for 30–40 min/session and 3 times/week. The total duration of exercise is 120–150 min/week.

Control group:

No restriction will be applied in terms of the mode of exercise, and participants can select their preferred exercise regimens during the trial. They will be asked to avoid making changes in their exercise habits.(4)Laboratory indicators

Weight, body fat, waist circumference, hipline, blood pressure, blood glucose, routine blood test, urine routine test, and renal and liver functions will be assessed. The body composition will be determined by BIA.(5)Follow-up

Follow-up will be conducted at baseline, 6 weeks ± 3 days, and 12 weeks ± 3 days.(6)Data and specimen collection

Participants’ demographic data will be collected in terms of age, gender, blood pressure, course of the gout, history of medications, etc. Participants will be followed up for three times (baseline, 6 weeks, and 12 weeks after the test) to measure height, weight, body fat, waist circumference, hipline, BMI, blood routine (e.g., sUA), urine routine (including urinary pH), and biochemical indices (blood glucose, serum insulin, triglycerides (TG), total cholesterol (TC), low-density lipoprotein cholesterol (LDL-C), high-density lipoprotein cholesterol (HDL-C), serum creatinine (SCr), and estimated glomerular filtration rate (eGFR)). Predictors of relevant systems will be evaluated after 12 weeks. Biological specimens will be destroyed after testing.

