### Criteria for discontinuing or modifying allocated interventions {11b}

#### Criteria for discontinuing

Participants withdraw the trial spontaneously.Pregnancy (pregnant participants should withdraw the trial).Adverse events that persuade investigators to urge participants to leave the trial as early as possible.Poor compliance of participants with the research program, and exercise adherence rate is not in the range of 80–120%.Occurrence of serious adverse reactions related to exercise intervention.In this study, major mistakes are detected in the clinical research program, making it difficult to evaluate the efficacy of the intervention. In addition, a significant deviation is observed in the implementation of a well-designed program.

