### Strategies to improve adherence to interventions {11c}

To increase participants’ compliance in the test group, it will be essential to record details of exercise (including date, start/end time, and rate) and take screenshots to retain data by the mobile phone application. Participants’ details of exercise in the control group will be recorded according to their exercise habits. Data from both groups will be forwarded to research team every week. Weekly telephone follow-up will be performed to strengthen participants’ compliance and to provide a recommendation sticking to an exercise program.

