#### Adverse event reporting and harms {22}

In this study, if a lot of exercise leads to excessive production of lactic acid, which can easily lead to the formation of urate crystals and induce gout flares. Ankle sprain, injury, and other conditions may occur during exercise. For obese or overweight people with gout, vigorous anaerobic exercise should be avoided, and stretching should be carried out before exercise to prevent injury.

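### Three weekly sessions of 30–40 min make 90–120 min, not the stated 120–150 min, and frequency is 3 per week in two places but 3–5 in a third

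*Protocol article*

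**What the plan says.** The protocol article gives the dose for the exercise group three times.

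- Abstract, Methods: the programme "will be conducted for 30–40 min/session and 3 days/week for 12 weeks". No weekly total is given.
- Intervention description {11a}: "it is recommended to exercise for 30–40 min/session (excluding warm-up and stretching), 3–5 times/week, and maintain 120–150 min/week".
- Research procedures, item (3), Program: "The exercise will be performed for 30–40 min/session and 3 times/week. The total duration of exercise is 120–150 min/week".

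Two other places depend on this dose. Objectives {7} names the aim as "the effects of a specific aerobic exercise program on body composition". The discontinuation criteria under {11b} include "Poor compliance of participants with the research program, and exercise adherence rate is not in the range of 80–120" per cent, and the article does not say which dose counts as 100%.

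**The concern.** In Research procedures, the weekly total should follow from the session length and frequency in the sentence before it. It does not. The frequency itself also changes between sections while the session length stays the same.

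The dose is the intervention in this trial. Three hospitals will prescribe it, and participants will carry it out in parks, gyms and similar places. A clinician working from the session rule could prescribe 90 minutes a week, and one working from the weekly total could prescribe 150. Each could cite the same paragraph. Any later report of dose delivered or of adherence needs a single prescribed figure to compare with.

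**Working it through.** **Inputs**, all from the protocol article:

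| Place | Sessions per week | Minutes per session | Weekly total (min) |
|---|---|---|---|
| Abstract, Methods | 3 | 30–40 | not given |
| Intervention description {11a} | 3–5 | 30–40, without warm-up and stretching | 120–150 |
| Research procedures, (3) | 3 | 30–40 | 120–150 |

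**Step 1. Try to reproduce the stated total in Research procedures.** Weekly minutes = sessions × minutes per session.

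- Lower end: 3 × 30 = 90, against 120 stated.
- Upper end: 3 × 40 = 120, against 150 stated.

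The figure is not reproduced. The ranges 90–120 and 120–150 share one value, 120. To span 120–150 with three sessions, each would have to last 120/3 = 40 to 150/3 = 50 minutes.

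**Step 2. Test {11a} in the same way, taking its total as excluding warm-up.**

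| Sessions | Product (min/week) | Part within 120–150 |
|---|---|---|
| 3 | 90–120 | 120 only (3 × 40) |
| 4 | 120–160 | 120–150 (4 × 30 to 4 × 37.5) |
| 5 | 150–200 | 150 only (5 × 30) |

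{11a} is therefore workable if the weekly total binds and the number of sessions may rise to four or five. Research procedures does not allow that, because it fixes three.

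**Step 3. Try a total that includes warm-up and stretching.** Let w be the minutes of warm-up and stretching per session. The article gives no value for w, so it has to be assumed. For three sessions to span 120–150:

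- lower end: w = 120/3 − 30 = 10;
- upper end: w = 150/3 − 40 = 10.

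Both ends give w = 10, so an allowance of 10 minutes reconciles Research procedures exactly: 3 × (40 to 50) = 120–150. It also fits {11a} at three sessions. At the other frequencies that {11a} allows, it gives 4 × (40 to 50) = 160–200 and 5 × (40 to 50) = 200–250, both above 150.

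**Step 4. Size of the gap if the total excludes warm-up.** 120 − 90 = 30 and 150 − 120 = 30 minutes a week, or 30 × 12 = 360 minutes over the 12 weeks. If the total includes 10 minutes per session, the gap is zero.

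**Step 5. Illustration for the adherence rate.** Suppose the rate were minutes done over minutes prescribed, without warm-up. Then 3 × 30 = 90 minutes scores 90/90 = 100% against a 90-minute reference and 90/120 = 75% against a 120-minute reference. The second falls below the 80% limit. The article does not say that the rate is computed in minutes or against either figure, so this shows only that one reference is needed.

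**The case against.** The strongest defence is that session length, frequency and weekly total are meant to apply jointly. A schedule of 3 × 40 = 120 minutes then meets every statement in all three places. The Abstract and Research procedures, which say what will be done, agree on three a week, and {11a} words its range as a recommendation. The target intensity of 60% of heart rate reserve is the same wherever it is stated. This stands to the extent that the statements do not exclude one another. Even so, 120–150 would shrink to a single value at three sessions a week, which is not what a stated range conveys.

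A second defence is that the total includes warm-up and stretching. The article does expect such time, since under {22} "stretching should be carried out before exercise to prevent injury". This reading is possible and would remove the arithmetic gap, but the text does not state it. The only place that mentions the distinction, {11a}, excludes warm-up from the session and gives the weekly total in the same sentence. Three against three to five sessions would still be unresolved.

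A reader might infer three stronger conclusions, which the documents do not support.

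- *No reading can reconcile the sections.* If any overlap counts as a fit, both readings fit {11a} and Research procedures at three sessions. If every permitted combination must fit, both fail for {11a}. Only a change of test between the readings would make one look worse than the other.
- *Participants doing 3 × 30 minutes would be discontinued for poor adherence.* The article does not define the denominator of the rate, and an article may leave that to the full protocol. The criterion also joins the rate to poor compliance.
- *The treatment comparison is biased.* Nothing in these statements affects the randomised comparison by intention to treat.

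**Conclusion.** The concern holds as an inconsistency in the stated dose, of minor severity. Two facts need no assumption: three sessions of 30–40 minutes make 90–120 minutes, next to a printed total of 120–150, and the frequency is three a week in two places and three to five in the third. The shortfall of 30 minutes a week holds only if the total counts the same minutes as the session. The adherence percentages are illustrative and do not support the severity. The trial is described as exploratory, and its exercise logs allow the delivered dose to be reported whatever was prescribed. The correction is still worth making, because the figures define the intervention under test and a fuller document cannot make the published sentences agree.

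**What to change.** State one dose, identically, in the Abstract, Intervention description {11a} and Research procedures. Either option is coherent:

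- **(a) Three sessions a week.** 30–40 minutes per session, with a weekly total of 90–120 minutes excluding warm-up and stretching. If 120–150 was meant to include them, keep that figure, label it so and state the allowance (10 minutes per session would match). Change {11a} from 3–5 to 3 sessions a week.
- **(b) Three to five sessions a week.** 30–40 minutes per session, with 120–150 minutes a week excluding warm-up and stretching as the binding weekly target, for example four sessions of 30 to 37.5 minutes. Change the Abstract and Research procedures from 3 to 3–5 sessions a week.

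In {11b}, name the chosen dose as the 100% reference for the 80–120% adherence rate, counted in the same way, with or without warm-up.

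The cost is wording in three places and one sentence in {11b}. No new data are needed, because under {11c} participants in the exercise group already "record details of exercise (including date, start/end time, and rate"). It would help to tell them whether the logged times should include warm-up and stretching.
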